### Participants and procedure

#### Inclusion criteria for baseline analysis (Fig. ***1***)

These are outlined in Fig. 1. For Study I, participants must have either type 1 or type 2 diabetes. For Study II, participants must have type 2 diabetes. For both studies, participants must be aged 18–59 years, have had diabetes for at least 1 year and must provide signed informed consent.

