### Primary and secondary outcome measures

In both studies, the primary outcome measure is the change in depression symptoms. Secondary outcome measures are changes in alexithymia and anxiety symptoms and self-image measures; changes in HbA1c concentration and midnight salivary cortisol concentration; use of antidepressants, and incidence of diabetes complications and mortality.

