#### Study I

If we assume that the standard deviation for the individual changes in Hospital Anxiety and Depression Scale – depression subscale in this study is 2.8, a change of 1.4 points represents half the standard deviation, which is considered indicative of clinically relevant changes in subjective symptoms [52]. Calculating a statistical power of 80 %, and assuming significance at the 0.05 level, 64 persons in each intervention arm are required at follow-up in a two-arm randomized controlled trial. Unfortunately we only recruited around 21 persons in each arm in Study I, rendering a power of 37 %.

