#### Study II

The power calculation is based on an analysis of variance (ANOVA), where two groups have the same means and one differs with 1.4 points, using the same standard deviation (2.8) as in Study I. Calculating a statistical power of 80 %, calculated using an ANOVA, 60 persons are required. However, using the Kruskal–Wallis test reveals that it is necessary to increase this by 15 %; thus, 70 persons are required in each arm in a three-arm randomized controlled trial.

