#### Studies I and II

In the previously mentioned intervention with ASSA, approximately 10 % of participants did not answer the self-report instruments after the intervention [32]. If we assume the same answering rate, 10 % more patients have to be included in each arm.

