#### Studies I and II

A paired-samples *t* test will be used for continuous and normally distributed variables (HbA1c concentration). The associations between outcome variables and baseline characteristics will be modelled using linear regression analysis (HbA1c concentration, midnight salivary cortisol concentration, psychological symptoms); logistic regression analysis will be used for categorical outcomes (incidence of diabetes complications and use of antidepressants).

Cox proportional-hazards regression will be used to analyze effects on mortality. Missing values of the self-report instruments will be imputed using multinomial logistic regression on the other variables in the same subgroup [53]. Imputation will be performed for the depression and anxiety subscales of the Hospital Anxiety and Depression Scale if there are at most two missing items for each subscale; for the 20-item Toronto Alexithymia Scale if there is at most one missing item for each subscale (‘difficulty identifying feelings’, ‘difficulty describing feelings’ and ‘externally oriented feelings’) and for the Structural Analysis of Social Behavior tool if there is at most one missing item for each of the eight clusters. Statistical significance will be considered for *P* < 0.05.

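### Cox regression is fixed as the analysis of mortality effects, but Study I may well have an arm without deaths and Study II has low power: deaths by arm should be the main mortality result

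*Protocol article*

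**What the plan says.** The statistical analysis section for Studies I and II commits both trials to one method: "Cox proportional-hazards regression will be used to analyze effects on mortality". The general significance threshold of 0.05 closes the same section. The outcome section ends its list of secondary outcomes with "use of antidepressants, and incidence of diabetes complications and mortality", and deaths are taken from the national causes of death register at T4.

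On size, the power section reports for Study I: "Unfortunately we only recruited around 21 persons in each arm in Study I". For Study II it states that "70 persons are required in each arm in a three-arm randomized controlled trial", counted at the last follow-up, and adds 10% for questionnaire non-response. Study I's T4 is 7 years after baseline; Study II runs from 2016 to 2023. On entry, "participants must be aged 18–59 years", and end-stage renal disease, cancer, hepatic failure and stroke are among the exclusions.

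The article gives no death rate, expected number of deaths, target hazard ratio or power for mortality. It does not say who enters the Cox model.

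**The concern.** A Cox hazard ratio comparing two arms has a finite maximum-likelihood estimate only if both arms have deaths. If one has none, the estimate runs to zero or infinity, its standard error explodes and the Wald P value carries no information. Small arms, entry below age 60 and the exclusion of several high-mortality conditions make few deaths likely.

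At stake is how a named secondary outcome will be reported. The sentence promises an analysis of effects. The data may give no finite hazard ratio, or one with an interval so wide that a non-significant P value could be taken as evidence that the interventions do not affect mortality. The article admits low power in Study I for depression but attaches no such caution to mortality.

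**Working it through.** **The plan's own figures.** No mortality figure is stated, so the depression figures serve to settle the test convention. With "a change of 1.4 points represents half the standard deviation" (SD 2.8), "assuming significance at the 0.05 level" and 80% power, n per arm = 2 × (1.960 + 0.842)² × (2.8/1.4)² = 62.8, so 63; the t-test version gives 64, as stated. At 21 per arm, power = Φ(0.5 × √(21/2) − 1.960) = Φ(−0.340) = 36.7%, against the stated 37%. A one-sided test would give 49%. A two-sided 0.05 level is therefore used below.

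**Inputs.** From the article: 21 per arm (Study I); 70 per arm at last follow-up (Study II), or 77 to 78 included (70 × 1.10 = 77; 70/0.90 = 77.8); 7 years, which for Study II is an upper limit. Assumed, because the documents give none: death rates r of 0.25% to 3% per year, constant and, unless stated, equal in all arms.

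**Study I: chance of an arm without deaths.** The probability that an arm of n has none is q = exp(−7rn). With two equal arms, the chance that at least one has none is 1 − (1 − q)².

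- r = 0.5%: q = exp(−0.735) = 0.480; chance 1 − 0.520² = 73%
- r = 1%: q = exp(−1.47) = 0.230; chance 1 − 0.770² = 41%
- r = 2%: q = exp(−2.94) = 0.053; chance 1 − 0.947² = 10%

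At 0.25% it is 90% and at 3% it is 2%; it reaches 50% at about 0.84% per year. If one arm's hazard is truly half the other's, the three figures rise to 84%, 60% and 27%.

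Sensitivity to the denominator: if counting refusers in their allocated arm doubled the arms to 42 (an illustration; the number is not given), the equal-rate chance is 41% at 0.5% per year and 10% at 1%.

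**Study II: chance of an arm without deaths.** With three arms of 70 the chance is 1 − (1 − q)³.

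- r = 0.5%: q = exp(−2.45) = 0.086; chance 24%
- r = 1%: q = exp(−4.9) = 0.0074; chance 2%
- r = 1.5% or more: under 1%

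**Deaths needed.** For a hazard ratio of 0.5 with equal arms, Schoenfeld's formula gives (1.960 + 0.842)²/(0.25 × (ln 0.5)²) = 7.85/0.120 = 65.3, so 66 deaths (Freedman: 71). Study I has about 42 participants. One 70 v 70 comparison in Study II would need 66 of 140 people (47%) to die.

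**Power at the assumed rates.** Expected deaths in a pair with hazard ratio 0.5: d = n × [(1 − exp(−7r)) + (1 − exp(−3.5r))]. Power = Φ(√d/2 × ln 2 − 1.960), which is only a rough guide when d is small.

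| r per year | Study I, 21 v 21: d, power | Study II, 70 v 70: d, power |
|---|---|---|
| 0.5% | 1.1, 5% | 3.6, 10% |
| 1% | 2.1, 7% | 7.1, 15% |
| 2% | 4.2, 11% | 13.9, 25% |
| 3% | 6.1, 13% | 20.2, 34% |

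With 78 per arm in Study II, power at 3% per year is 38%.

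**The descriptive alternative always returns a result.** An arm of 21 with no deaths over 7 years has 147 person-years; the exact two-sided 95% upper limit is −ln(0.025)/147 = 2.5% per year.

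**The case against.** Mortality is listed last among the secondary outcomes and no power is claimed for it, Cox regression is the conventional choice for register survival data, and handling of sparse events is often left to a fuller document. All of that stands. Nothing here is miscalculated, and low power for a secondary outcome is not in itself a fault.

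A reader might go further and infer that Cox regression is unusable in both trials. The documents do not support that. In Study II an arm without deaths is unlikely at about 1% per year or more, and one empty arm would still leave the contrast between the other two estimable. In Study I the failure depends on a rate the article does not give. The age limit and exclusions point downwards; the high HbA1c and psychological symptoms, which the background links to complications and mortality, point upwards.

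Nor is every P value lost when an arm is empty. With 0 v 6 deaths in 21 v 21 and no censoring before the sixth death, the score (log-rank) test gives P = 0.009 and the likelihood-ratio test P = 0.002; penalised likelihood gives a finite hazard ratio. Only the ordinary estimate and its Wald test fail.

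A reader might also take 42 and 210 people as the Cox analysis set. The article does not say so. Refusers in Study I had already been allocated, 77 to 78 per arm would be included in Study II, and mortality is also sought for the other groups followed. Larger randomised denominators lower the chance of an empty arm. Comparisons with patients who refused or did not meet the criteria, taken as separate groups, are not randomised and could not carry an effect claim.

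What survives is narrower: the article does fix the method and its aim, and the power limit holds at every rate examined.

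**Conclusion.** The point holds as a limit on interpretation. In Study I, with about 21 per arm, the chance of no finite hazard ratio is about 73%, 41% or 10% at assumed death rates of 0.5%, 1% or 2% per year, and lower if refusers are counted as allocated. In Study II the model will usually be estimable at about 1% per year or more, but pairwise power for a halved hazard is about 10% to 34% over 0.5% to 3% per year with 70 per arm, and at most 38% with 78. These figures rest on the assumed constant rates and a full 7 years; shorter follow-up in Study II would mean fewer deaths and less power.

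It would be too strong to call this a sample-size error, or to conclude that mortality must be dropped or demoted. The depression figures reproduce, and the article makes no power claim for mortality. The change is worth making because the fixed method can degenerate in Study I and, in either study, a non-significant result would say little.

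**What to change.** Replace the Cox sentence in the statistical analysis section for Studies I and II with text to this effect: deaths will be reported for all randomised patients, by allocated arm, as counts and rates per person-year with exact 95% confidence intervals, and this is the main mortality result; any Cox model is exploratory and uses penalised (Firth) likelihood or likelihood-ratio inference where an arm has few or no deaths; a non-significant result will not be interpreted as absence of an effect on mortality.

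Mortality can remain a secondary outcome, so the abstract, objectives and outcome section need no change. Register collection at T4 is the same, provided that patients who refused after allocation are kept under their allocated arm for this outcome. The cost is a few lines of text, and the small downside is that no confirmatory test of mortality is made.

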### Self-report instruments

#### Studies I and II

The Hospital Anxiety and Depression Scale will be used at all measuring points to assess self-reported anxiety and depression [4, 5, 32, 37–39]. The cut-off level for each subscale recommended by the constructors of this scale (≥8 points) will be used for inclusion in the intervention [38]. In a study that compared the Swedish version of the Hospital Anxiety and Depression Scale with a structured clinical interview for DSM-III criteria, the optimal cut-off level for screening was ≥5 points for both subscales [39].

The 20-item Toronto Alexithymia Scale will be used at all measuring points to assess alexithymia [4, 19, 32, 37, 40–42]. This scale consists of 20 statements rated from 1 to 5, and is based on three subscales: ‘difficulty identifying feelings’ (seven statements), ‘difficulty describing feelings’ (five statements) and ‘externally oriented feelings’ (eight statements).The recommended cut-off level (≥61 points) will be used for inclusion in the intervention [41, 42].

The affinity dimension of the Structural Analysis of Social Behavior assessment tool will be used to assess self-image [23, 35, 43]. This test consists of 36 statements with response options on a scale between 0 and 100; the results are summarized into eight clusters. High scores for the clusters ‘blaming self’, ‘hating self’ and ‘ignoring self’; and low scores for the clusters ‘accepting self’, ‘loving self’ and ‘nourishing self’ form a negative self-image. A negative self-image is defined as results below 284 points. The Structural Analysis of Social Behavior test will be used at T0 and at T4.

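### Missing questionnaire items are imputed with an unordered (multinomial) model that does not suit ordered or 0-100 items and is unstable at Study I's T1 and T2; a minor point with a one-sentence fix

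*Protocol article*

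**What the plan says.** The Statistical analysis section, under Studies I and II, gives a single item-level rule: "Missing values of the self-report instruments will be imputed using multinomial logistic regression on the other variables in the same subgroup". It then limits when the rule applies. For each HADS subscale, items are imputed "if there are at most two missing items for each subscale". For TAS-20 the limit is one missing item per subscale. The self-image tool is covered explicitly: "for the Structural Analysis of Social Behavior tool if there is at most one missing item for each of the eight clusters".

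The Self-report instruments section describes the items. Of TAS-20 it says: "This scale consists of 20 statements rated from 1 to 5, and is based on three subscales", with seven, five and eight statements. Of the self-image tool it says: "This test consists of 36 statements with response options on a scale between 0 and 100; the results are summarized into eight clusters". The same section places the self-image tool at T0 and T4 only, while HADS and TAS-20 are used at every measuring point. HADS item count and scoring are not given.

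On size, the power section states: "Unfortunately we only recruited around 21 persons in each arm in Study I". According to the Schedule for assessments, in Study I only the two intervention groups are assessed at T1 and T2; nonparticipants (Groups 3 and 4) are assessed at T0 and T4.

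**The concern.** A multinomial logit fits a separate equation for each response option except one and uses no information about their order. For graded items that spends many parameters on something the scale already supplies. With few patients, some coefficients run off towards infinity (separation) and the prediction for the missing item becomes erratic.

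HADS depression change is the primary outcome in both studies, so imputed items enter it. If the fit fails in Study I, the analyst must choose a substitute after seeing the data. The rule also does not say whether the most likely category, a random draw or the expected value is imputed, and these behave differently.

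**Working it through.** **The plan's own figures.** The article gives none for imputation. Its Study I power inputs reproduce, which confirms the patient number and standard deviation used below:
- n per arm = 2 × (1.96 + 0.84)² × 2.8² / 1.4² ≈ 63; the t test gives 64, as stated.
- At 21 per arm: 1.4 / (2.8 × √(2/21)) = 1.62; 1.62 − 1.96 = −0.34; power ≈ 37%, as stated.

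**Available patients.** Study I at T1 and T2: 2 × 21 = about 42 at most. Study II at target: 3 × 70 = 210.

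**Coefficients.** 'Subgroup' is read as subscale or cluster, the units in which the limits are set. With K response options and p other items as linear predictors, a multinomial logit needs (K − 1)(1 + p) coefficients; an ordinal (proportional-odds) logit needs (K − 1) + p.

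| Items | K | p | Multinomial | Ordinal |
|---|---|---|---|---|
| HADS subscale (assumed 7 items, 0-3) | 4 | 6 | 3 × 7 = 21 | 9 |
| TAS-20, 5 items | 5 | 4 | 4 × 5 = 20 | 8 |
| TAS-20, 7 items | 5 | 6 | 4 × 7 = 28 | 10 |
| TAS-20, 8 items | 5 | 7 | 4 × 8 = 32 | 11 |

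Self-image clusters average 36/8 = 4.5 items, so 4 or 5. In steps of 10 (K = 11, assumed) the model needs 10 × 4 to 10 × 5 = 40-50 coefficients. If any integer is allowed (K = 101, assumed), it needs 100 × 4 to 100 × 5 = 400-500.

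**Accuracy.** One-factor ordinal items were simulated with one item missing. Loadings and answer distributions are assumptions. RMSE per missing item at n = 42:

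| Items | Most likely category | Expected value | Person mean | Excess of expected value |
|---|---|---|---|---|
| HADS-like | 1.10 | 0.97 | 0.79 | 0.97/0.79 = 23% |
| TAS-like, 7 items | 1.47 | 1.28 | 1.11 | 1.28/1.11 = 15% |
| TAS-like, 8 items | 1.69 | 1.47 | 1.24 | 1.47/1.24 = 19% |
| HADS-like, unequal items | 1.11 | 0.97 | 0.87 | 0.97/0.87 = 11% |

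A separate HADS-like simulation gave 1.00 for the expected value against 0.83-0.85 for the person-mean or linear rule (18-20%). In the unequal-item setting an ordinal logit's expected value scored 0.86, so like for like the multinomial form loses 0.97/0.86 = 13%.

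Near-separation (a coefficient above 15 in absolute value) at n = 42 occurred in 65% of HADS-like fits and 44-46% of TAS-like fits. If 'subgroup' meant a treatment arm, n would be about 21 and the figure 95-99%.

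**Larger samples.** At n = 200 separation falls to 0-4%. The expected-value form is then about equal to the person mean: 0.78 against 0.77 (HADS-like), 1.10 against 1.09 and 1.25 against 1.24 (TAS-like). At n = 210 it was 0.85 against 0.84. The most likely category stays worse at n = 200: 0.92 against 0.77 with bias −0.19 (HADS-like), and 1.36 against 1.09 with bias −0.28 (TAS-like, 7 items). The bias is towards the commoner, low answers.

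**Trial-level effect.** The item non-response rate is not stated; assume 5-10% of patients miss one HADS item at one visit. Taking the unfavourable case of a random draw (RMSE 1.16) against a linear rule (0.83), the added variance at 5% is 0.05 × (1.16² − 0.83²) = 0.033. Against a change-score variance of 2.8² = 7.84 that is 0.4%; at 10% it is 0.8%.

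**The case against.** The strongest reply is that the choice hardly matters: the article caps imputation at one or two items per subscale, and the added variance is under 1% in the illustration. That stands, and it sets the grade. A second reply is that the rule follows a cited source and that an article leaves pooling of visits, grouping of sparse categories or a fallback to the full plan. That holds for those details. The model itself, however, is fixed here for all three instruments.

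Four stronger readings are tempting but not supported:
- A reader might infer that ignoring order raises error by 20-45% throughout. Such figures arise when a random draw or a most likely category is set against a conditional mean. Draws are not meant to minimise RMSE: a draw from an ordinal model scores almost the same as one from the multinomial model (1.16 against 1.19 at n = 42; 1.15 against 1.14 at n = 210).
- A reader might call the Study I imputations close to arbitrary. At n = 42 the most likely category had RMSE 1.15, against 1.59 for a truly arbitrary category.
- A reader might apply n = 42 to the self-image tool or the entry cut-offs. The tool is used only at T0 and T4, when Groups 3 and 4, of unstated size, are also assessed. The cut-offs apply at T0, and the article does not say that imputed scores decide entry.
- A reader might take several hundred self-image coefficients as fact. That rests on an integer step the article does not state.

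It is also fair that a regression or person mean understates the variance of imputed items slightly.

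**Conclusion.** The point holds as a minor correction. The rule applies an unordered model to graded items. For HADS and TAS-20 at T1 and T2 of Study I it is unstable and loses about 15-20% in RMSE against a person-mean or linear rule even in its most favourable, expected-value form; individual settings ranged from 11% to 23%. At Study II's target size there is no material loss unless the most likely category is imputed. For self-image items the model is mismatched in kind, but how badly it would fit depends on the step width and on how many patients in Groups 3 and 4 enter the fit, neither of which is stated. The primary result is not threatened, and the stated sample size and power do not change.

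This rests on the assumed HADS format, the simulated loadings and answer distributions, and reading 'subgroup' as subscale or cluster.

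**What to change.** In the Statistical analysis section, replace the multinomial rule with one that respects the scale, and keep the stated limits (two missing items per HADS subscale, one per TAS-20 subscale, one per self-image cluster). Either of these would do, if one is named in advance:
- the mean of the patient's answered items in the same subscale or cluster at that visit; or
- linear regression of the missing item on that mean, truncated to the item's range.

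The first needs no model fit and so cannot fail in Study I. The second allows for items that differ in average level.

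The cost is one sentence and less programming than the present rule. Imputed items may be non-integer, their variance is slightly shrunk, and the rule departs from the cited method.

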## Discussion

Diabetes is a progressive and demanding chronic disease, which requires emotional adaptation [1]. Previous research has shown that alexithymia is a risk factor for depression [15], which is deleterious for patients with diabetes [4–7]. Also, a deficit in the awareness of affects results in abnormal physiological reactions and impaired capacity for self-care [13]. An advanced capacity for self-care is necessary in diabetes.

For this reason, we were interested in finding interventions focusing on increased emotional awareness and verbal expressiveness. We have chosen to test the ASSA [30, 32, 37] against BBAT [34–36] in two studies. In Study I, we perform a two-arm randomized controlled trial with patients with type 1 or type 2 diabetes from one hospital diabetes outpatient clinic. In Study II, ASSA, BBAT and ‘treatment as usual’ will be compared in a three-arm randomized controlled trial for patients with type 2 diabetes from primary care units.

We expect the ASSA method to be more efficient than BBAT in reducing depressive symptoms. In the ASSA intervention, patients are systematically trained to identify and describe feelings, and are also presented with advanced affect theory. In BBAT, patients focus more on bodily features, such as breathing, grounding, stability, centring, flexibility and flow [36]. The patients undergoing BBAT are not systematically trained to identify and describe feelings but they are encouraged to observe and accept sensations and emotions that awaken during the treatment sessions [36]. As neither of the two interventions is ‘placebo’, we think it is important to compare both ASSA and BBAT with treatment as usual.

We have chosen reduction of depression symptoms as the primary outcome measure, even though some patients were not depressed at the time of inclusion. A reduction in depression symptoms might be of value even for patients not fulfilling our criteria for self-reported depression. A lower cut-off level (≥5 points) has been proposed for the depression subscale of the Swedish version of Hospital Anxiety and Depression Scale than we have chosen to use. This means that the sensitivity for depression might be less than optimal in our study [39].

One limitation to our studies is that we only use self-report instruments, not structured interviews. Another limitation is that not enough patients in the first part of our randomized controlled trial agreed to participate in the intervention, so randomizing into three arms (ASSA, BBAT and a no-intervention group) was impossible. We aim to recruit more patients in Study II, to be able to perform the three-arm randomized controlled trial.

We foresee recruitment difficulties. Patients have generally not previously been introduced to the idea that emotional factors might impact their disease; presumably neither ASSA nor BBAT are methods known to the patients. Patients may feel that it is stressful to talk about emotions in a group situation and therefore BBAT may be more easily accepted.

Another difficulty is that most patients are working or university students, which might make participation difficult, therefore the Swedish Social Insurance Agency will offer preventive sick-leave compensation for treatment session time. It is, however, not possible to offer preventive sick-leave compensation for nonparticipants.

The clustering within the pair of instructors in ASSA might affect the results, but this will be tested. The three ASSA instructors were trained together, and have previously been ASSA instructors together in all three possible combinations; this will probably minimize the effects of clustering. The three BBAT instructors all have special training and long experience, but have not been trained together; however, they will co-operate in synchronizing how they will perform the BBAT intervention. The results of the interventions might be influenced by the group members being randomized into each group and by study design. Previously, we have carefully selected patients who we thought could benefit from the ASSA intervention and would not disturb the group dynamics. In the current studies, no individual selection can be made by the instructors, owing to the study design. Previously, we have made contracts with the patients to do their very best to participate in all sessions. In the current studies, we have declared that they can stop participating at any time.

In summary, depression is a serious disease in patients with diabetes. Intervention with ASSA and BBAT will be tried for patients with diabetes, psychological symptoms and inadequate glycemic control, first in one two-arm randomized controlled trial and then in one three-arm randomized controlled trial.

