#### Intervention criteria

For both studies, these are either a HbA1c concentration of at least 62.5 mmol/mol or at least one of: self-reported depression, anxiety, alexithymia or a negative self-image (Fig. 1).

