#### Randomization and allocation

The randomization and allocation of the coded patients will be performed by an independent statistician with the purpose of having as equal distribution as possible of sex and age in each intervention arm.

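### Baseline HADS-D probably predicts the primary outcome strongly, yet Study II neither balances on it nor adjusts for it, which costs precision but not validity

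*Protocol article*

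**What the plan says.** Under Primary and secondary outcome measures, for both studies, "the primary outcome measure is the change in depression symptoms". Depression is not required for entry. The Intervention criteria ask for "either a HbA1c concentration of at least 62.5 mmol/mol or at least one of: self-reported depression, anxiety, alexithymia or a negative self-image". The abstract words this differently, listing the HbA1c criterion together with a psychological one, but on either reading a patient can enter without depression. The Discussion confirms that this happened ("We have chosen reduction of depression symptoms as the primary outcome measure, even though some patients were not depressed at the time of inclusion") and defends it: "A reduction in depression symptoms might be of value even for patients not fulfilling our criteria for self-reported depression".

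HADS-D is known before allocation, because it is part of T0 and helps decide eligibility. Self-report instruments: "The cut-off level for each subscale recommended by the constructors of this scale (≥8 points) will be used for inclusion in the intervention". Allocation is nevertheless done only "with the purpose of having as equal distribution as possible of sex and age in each intervention arm".

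The sample size applies one effect to everyone: "a change of 1.4 points represents half the standard deviation, which is considered indicative of clinically relevant changes in subjective symptoms". The standard deviation of 2.8 comes from an earlier study of the affect school method in chronic benign pain. The Statistical analysis section compares changes in psychological symptoms by rank tests without covariates (Wilcoxon signed rank and Kruskal–Wallis in Study I, Kruskal–Wallis in Study II). It also plans linear regression of outcomes on baseline characteristics, but names neither arm nor baseline depression as a term.

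**The concern.** When entry does not depend on the outcome scale, baseline scores on it can range from near zero to clearly raised. High scorers can be expected to fall more, in every arm, through natural course and regression to the mean. Patients near zero can hardly fall at all. Two things follow.

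- Baseline HADS-D explains part of the spread in change scores. A design that neither balances on it nor adjusts for it leaves that part in the error term.
- Patients close to the floor cannot show a full 1.4-point reduction, so the observable average effect is somewhat smaller than the one the sample size assumes.

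The stake is precision in Study II. Its size of 70 per arm is already demanding, given that Study I reached about 21 per arm against 64 required. Study II had not begun recruiting when the article appeared, so its allocation could still be changed.

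**Working it through.** **Inputs from the article:** SD of change 2.8; effect 1.4; significance level 0.05; power 80 %; 64 per arm (Study I); 60, raised to 70, per arm (Study II). **Assumptions, not in the article:** HADS-D range 0–21; share q scoring 8 or more; extra fall g of those patients, the same in every arm; baseline means.

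**1. The plan's own figures reproduce.** Two arms: n = 2 × (1.96 + 0.84)² × (2.8/1.4)² ≈ 63; the t-test version gives 63.8, so 64. At 21 per arm, power is 36.7 % (normal) or 35.3 % (t), against 37 % stated. Three arms with means 0, 0, 1.4: f = 0.66/2.8 = 0.236, which needs 58.8 per arm against 60 stated; 60 × 1.15 = 69 against 70 stated. The arithmetic is sound.

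**2. Precision left unused (Study II, q = 0.4, total SD held at 2.8).** Total variance of change is 2.8² = 7.84. The part due to baseline stratum is q(1 − q)g² = 0.24g². The SE of a difference between two arms of 70 is √(2 × variance/70).

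| g (points) | Stratum part | Remaining variance | SE, ignoring baseline | SE, accounting for baseline | Equivalent n per arm |
|---|---|---|---|---|---|
| 1 | 0.24 | 7.60 | 0.473 | 0.466 | 70 × 7.84/7.60 = 72 |
| 2 | 0.96 | 6.88 | 0.473 | 0.443 | 70 × 7.84/6.88 = 80 |
| 3 | 2.16 | 5.68 | 0.473 | 0.403 | 70 × 7.84/5.68 = 97 |

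Simulation for g = 2 to 3 agrees: about 0.48 falling to 0.40–0.45. If g is only 1 point the gain is negligible.

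**3. Why balancing needs adjustment.** If arms are balanced on HADS-D but the test ignores it, the test still scales by 7.84 although arm means vary as if the variance were 6.88 or 5.68. For the three-arm test (chi-square, 2 df, critical value 5.99) the approximate type I error is exp(−5.99 × 7.84/(2 × 6.88)) = 3.3 % for g = 2 and exp(−5.99 × 7.84/(2 × 5.68)) = 1.6 % for g = 3. Simulation gives 1–3 %. The precision gained would be lost to a conservative test.

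**4. Validity without balancing.** In a simulated two-arm null (40 % depressed, extra fall 1–3 points, rank test) type I error is 4.7–5.2 %. With 30–50 % depressed, the chance that two arms differ by at least 20 percentage points in the depressed share is 13–16 % at 21 per arm and 1–2 % at 70.

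**5. Dilution by the floor.** Give every patient the full 1.4-point latent benefit and let only the bottom of the scale cut it.

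- Two arms of 64, assumed baseline means 8 down to 3: observed difference 1.29 down to 0.99, rank-test power 75 % down to 65 %.
- Three arms of 70, Kruskal–Wallis, assumed baseline means 7, 5 and 4: differences of about 1.28, 1.19 and 1.12, power about 83 %, 80 % and 77 %. Rounding scores to integers lowers the last two powers by about two points. Part of the loss is hidden by the reserve of 70 over the 58.8 that ANOVA needs.

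**6. What an estimate in the 8-or-more stratum could deliver.** At 25–50 % of 70 there are about 18–35 patients per arm. ANOVA power for 1.4 points is about 30–56 %. The 95 % half-width for two arms is 1.96 × 2.8 × √(2/n) = 1.83 (n = 18) to 1.31 (n = 35).

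**The case against.** The broad population is a disclosed and reasoned choice. The aims concern patients with psychological symptoms and poor glycaemic control, not depressed patients, so the overall comparison answers the stated question. The article itself reports that a Swedish validation study found 5 points the better screening cut-off, so scores of 5–7 may be symptomatic, and a patient scoring 2–7 has room to fall 1.4 points. An unseen analysis plan may already contain baseline adjustment. All of this stands. It is why the population should stay as it is, and why the point rests on the balancing factors and tests that the article does state.

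Three stronger readings are tempting and are not supported.

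- A reader might infer that chance imbalance in depressed patients can mimic a benefit. Randomisation holds type I error near 5 %, and imbalance can hide an effect as easily as suggest one. The 95 % sampling margin between two arms of 70 is 1.96 × 0.473 = 0.93 points and, if 2.8 is the right SD for this mixed group, already includes it. Refusals after allocation are a separate matter.
- A reader might infer that power collapses far below 80 %. That needs zero benefit in everyone below 8, which nothing in the article says.
- A reader might infer that a separate result in depressed patients would settle a null overall finding. At 30–56 % power it would not.

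**Conclusion.** The point holds as a matter of efficiency. Patients may enter without depression, T0 HADS-D is available before allocation, and neither the allocation nor the stated tests use it. The planned test remains valid and the stated sample sizes are correct for their inputs.

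Under the assumptions in the working (40 % scoring 8 or more, extra fall 2–3 points), using baseline HADS-D would reduce the standard error by about 6–15 % (0.473 to 0.443 or 0.403), worth roughly 10 to 27 more patients per arm. The floor trims the observable effect modestly, to about 1.3–1.0 points under the assumed baseline means. Neither figure can be fixed, because the article gives neither the share scoring 8 or more nor the baseline distribution. With an extra fall of only 1 point, little would be gained. Study I is already allocated, so balancing can be changed only in Study II.

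**What to change.** For Study II:

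1. Add T0 HADS-D (8 or more versus below 8) to sex and age as a balancing factor in the independent statistician's allocation.
2. Compare HADS-D between arms adjusted for T0 HADS-D, for example by ANCOVA or rank ANCOVA. The continuous score also captures differences within the two strata. This step must accompany the first, or the test becomes conservative.
3. Keep the broad primary population. A descriptive between-arm estimate with 95 % CI in the 8-or-more stratum is optional and should be presented as imprecise.

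The cost is one more factor in an allocation not yet made when the article appeared, and a slightly more complex primary analysis. No extra data are needed. The adjustment recovers precision; it does not remove the floor, so some dilution of the 1.4-point effect remains.
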